### Strengths and limitations

The presented study design has several strengths. First, it is in line with ethical requirements that all adolescents are offered treatment. Waiting for 16 weeks in the WL condition still seems adequate given that adolescents may reside for up to 2 years in youth welfare institutions. In randomized clinical trials, for example, only cases may have received treatments. Second, it requires a smaller sample when participants become part of several analysis groups (intervention vs. WL). Third, alternative explanations of time effects may be controlled for by comparing BL-FU effects with PRE-BL effects.

Challenges arise from uncontrolled parallel treatments during the waiting period. Such treatments cannot be included in the quantitative estimation of treatment effects due to the limited number of participants in each group. Furthermore, homogeneity of cooperating youth welfare institutions is limited. Results may thus have to be replicated in other and diverging institutions. Although the sample size was *a-priori* calculated to maximize the use of available resources, drop-out rates may be unexpectedly high. In this case, additional participants and institutions may have to be recruited. In case of limited sample size, using Bayesan methods instead of testing for differences from zero may be advisable (74). Both the AUDIT and DUDIT have been previously used to assess changes in alcohol- and drug-related problems in adolescents and young adults using 3-month intervals between BL and FU (75, 76). Nevertheless, it remains possible that small changes in problems might go unnoticed given that both instruments cover 12 month periods. Another limitation arising from the limited sample size in a phase II study is the impossibility to adjust for several baseline variables. Such superior analysis strategies are not feasible at this point of the intervention development but will be imperative during phases III/RCT and phase IV studies in the future. The same holds true for the analysis of relevant patient subgroups (e.g., differentiating those with primarily alcohol-related problems from those with primarily cannabis-related problems) and intention-to-treat analyses or sensitivity analysis. Finally, additional measures that would objectify relapse to the use of alcohol or other drugs were not funded and will have to be implemented in a future trial, preferably a multi-center RCT testing DELTA-JU against treatment-as-usual.

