### Data analysis

Analyses will be conducted with the most recent version of the software “IBM SPSS Statistics,” currently version 27.0. Adolescents are analyzed as randomized if they participated in at least one DELTA session (DELTA condition only). To test all non-descriptive hypotheses (see below, hypotheses 2–4), a repeated measures MANOVA will be conducted using time as factor (“within factor”) given the explanatory nature of the trial and the non-importance of between-group effects. A significant reduction over time (BL vs. FU) in all *N* = 40 participants across all metric outcomes (MaCS score, FTND score, DUDIT score, AUDIT score, and cigarettes per day during the past month according to substance use interview) indicates a relevant intervention effect. This multivariate approach will limit the chance for false-positive results as otherwise possible due to multiple testing. Effect sizes will be classified into small effects (ƞ^2^ ≥ 0.01), medium effects (ƞ^2^ ≥ 0.06), and large effects (ƞ^2^ ≥ 0.14). In case of severe non-normality of outcome variables, we will have to apply non-parametric tests instead of the repeated measures MANOVA.

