#### Hypotheses

Aim (A) is reached when for each need, identified through qualitative analyses of interviews, one or more adjustments to the content or procedure of DELTA-JU is documented. No quantitative hypothesis is applicable. Aims (B) and (C) are achieved through testing the following hypotheses in adolescents who are abstinent for alcohol and drugs except nicotine/tobacco:
Adolescents: relevant increase in SUD-related subjective utility through FU (descriptive: a medium rating of 2.0 or higher in the respective GEJ items across participants);Adolescents: significant reduction of substance-related craving as a measure of relapse risk (*p* < 0.05, MaCS score) through FU;Adolescents: significant reduction of SUD severity (*p* < 0.05, scores of FTND, AUDIT, and DUDIT) through FU;Adolescents: significant reduction of self-reported past-month tobacco use through FU (*p* < 0.05, substance use interview);Personnel: relevant increase in SUD-related subjective utility through FU (descriptive: a medium rating of 2.0 or higher in the respective GEB items across participating personnel); andPersonnel: high satisfaction ratings concerning the workshop organization (descriptive: a medium rating of 4.0 or higher in the respective GEB items across participating personnel).

Additionally, secondary outcomes in adolescents (BDI-II, PQ-16, UCLA-PTSD, PSS-10, and SWLS) and personnel (ERI-S-10) will be tested exploratorily for changes through FU as previously done in the DELTA evaluation (15). All reductions through FU in adolescents are expected to be descriptively larger than reductions over the natural course, i.e., from PRE to BL in the WL group.

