#### Estimation of sample size

Sample size will be optimized to achieve sufficient power for hypothesis testing. Assuming an error probability of α = 0.05, test power of 1−β = 0.95, a large effect of time with *f* = 0.40, and a repeated measures correlation of *r* = 0.1, we computed minimum sample sizes of *N* = 40 analyzed adolescents and *N* = 40 analyzed personnel with the G*Power software (64). Large effect sizes were anticipated given that the actual intervention effect size (15) had not yet been analyzed at the time of the inception of DELTA-JU and the proposal for funding and ethics approval in 2020.

Considering the dropout rates from BL to FU for adolescents (assuming 20%) and personnel (assuming 10%), at least *N* = 50 adolescents and *N* = 45 personnel will have to be included at BL. In case that dropout rates exceed 20%, we will continue to sample participants in order to achieve the required analysis sample size of *N* = 40 nonetheless as long as study funding is available. For qualitative interviews, a sample size of *N* = 10 was deemed as an adequate compromise between resources and expected output.

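### Reusing waitlist adolescents saves headcount but adds little precision to the treated-versus-natural contrast, for which N = 40 was not sized and which is judged only descriptively

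*Protocol article*

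**What the plan says.** Estimation of sample size takes "Assuming an error probability of α = 0.05, test power of 1−β = 0.95" and "a large effect of time with *f* = 0.40, and a repeated measures correlation of *r* = 0.1", and reports that "we computed minimum sample sizes of *N* = 40 analyzed adolescents and *N* = 40 analyzed personnel with the G*Power software". After 20% dropout in adolescents this becomes 50 to be included.

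Data analysis applies that N to a repeated-measures MANOVA with time as the only factor, BL against FU, both arms pooled. The reason given is "given the explanatory nature of the trial and the non-importance of between-group effects". A significant reduction is read as a relevant intervention effect.

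The natural course enters only in Hypotheses: "All reductions through FU in adolescents are expected to be descriptively larger than reductions over the natural course", meaning PRE to BL in the waitlist group. No estimate, interval or expected precision is attached.

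Strengths and limitations then lists two benefits. The design is said to need fewer people ("it requires a smaller sample when participants become part of several analysis groups (intervention vs. WL")), and the BL-FU versus PRE-BL comparison is said to offer possible control of alternative explanations.

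**The concern.** The primary test has no control. A BL-FU reduction from natural course, regression to the mean or residence in the institution would count as an intervention effect. The PRE-BL comparison is the plan's only guard against that reading. Yet the sample size was not chosen for it, and its criterion is a bare comparison of two observed means.

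Read together, the two listed strengths suggest that entering waitlist adolescents in both comparison groups makes a small trial informative about treated versus natural change. The shared BL value works against this. A waitlist adolescent with a high BL by chance shows a small PRE-BL reduction and a large BL-FU reduction, so the two means are negatively correlated and their difference is noisier than two separate groups of 40 and 20 would give.

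**Working it through.** **Inputs.** From Estimation of sample size: α = 0.05, power 0.95, f = 0.40, r = 0.1, N = 40, dropout 20%. Assumed: 20 analysed per arm (the visible text gives no per-arm number; the sequence alternates between arms by institution), equal variances, no clustering. SD means the SD of a single measurement.

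**1. The plan's own figure.** For a within-person factor with m = 2 visits, λ = f²·N·m/(1−r). At N = 40, λ = 0.16 × 40 × 2/0.9 = 14.2, and power is 0.957. N = 39 already gives 0.952. So 40 reproduces as the size for a pooled time effect, and 40/(1−0.20) = 50. Reuse of the waitlist does not enter this calculation.

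**2. Headcount.** All 40 give a BL-FU change and about 20 also give a PRE-BL change: 60 changes from 40 people. Separate groups would need about 60 people.

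**3. Variance of the contrast.** Take the mean BL-FU reduction in all 40 minus the mean PRE-BL reduction in the 20 waitlist adolescents. Weights per person, each divided by 20, are:

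- waitlist: PRE −1, BL +1.5, FU −0.5 (sum of squares 3.5)
- immediate: BL +0.5, FU −0.5 (sum of squares 0.5)

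With one common correlation r, variance = (3.5 + 0.5)(1−r)/20 = 4(1−r)/20. A plain comparison of 20 immediate with 20 waitlist changes has variance 2(1−r)/20 + 2(1−r)/20 = 4(1−r)/20, which is the same. At r = 0.1 both are 0.18 SD². Simulation (100,000 runs) gave 0.1812 and 0.1813.

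With V the variance of one change, independent groups of 40 and 20 would give V/40 + V/20 = 0.075V, against 0.10V here. That is the 25% reduction a reader might expect from reuse.

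**4. Other weights and correlation patterns, 20:20.** Let w be the weight on the immediate arm's BL-FU mean. With equal correlations the total is [1 + (2−w)² + (1−w)² + 2w²](1−r)/20. It is smallest at w = 0.75: (1 + 1.5625 + 0.0625 + 1.125) = 3.75, ratio 3.75/4 = 0.9375.

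| Correlations | Weighting | Variance relative to plain 20 v 20 |
|---|---|---|
| Equal, any r | simple pooling | 1.000 |
| Equal, any r | optimal | 0.9375 |
| AR(1), r = 0.1 | simple pooling | 0.975 |
| AR(1), r = 0.1 | optimal | 0.924 |
| AR(1), r = 0.5 | simple / optimal | 0.875 / 0.859 |
| AR(1), r = 0.7 | simple / optimal | 0.825 / 0.819 |

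**5. Width at r = 0.1.** Largest variance: √0.18 = 0.424, and 1.96 × 0.424 = 0.83 SD. Smallest: 0.924 × 0.18 = 0.166, √0.166 = 0.408, half-width 0.80 SD.

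For scale, f = 0.40 over two visits is a difference of 0.8 SD. If that whole difference applied to the contrast, a 20 versus 20 comparison would exclude zero with probability 0.47 (normal) or 0.45 (t).

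**6. Sensitivity (equal correlations, simple pooling).**

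- r = 0.5: variance 0.10, half-width 0.62 SD.
- r = 0.7: variance 0.06, half-width 0.48 SD.
- 16 immediate and 24 waitlist, r = 0.1: variance 0.165 (ratio 0.88), half-width 0.80 SD.
- 24 immediate and 16 waitlist, r = 0.1: variance 0.2025 (ratio 1.08), half-width 0.88 SD.

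**7. The descriptive criterion.** If the programme has no effect and the natural trend is the same in both intervals, the contrast is symmetric about zero. Any one outcome then shows the larger BL-FU reduction about half the time.

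**The case against.** The strongest defence is that the sentence is about headcount and is true on that reading. The untreated comparator costs no extra people, and no precision is claimed for it. N = 40 is derived from α, power, f and r, without appeal to reuse. The contrast is openly descriptive, so a power figure for it tests something not planned and moves f = 0.40 onto a quantity it was not specified for. The article also concedes small groups, words the control of other explanations cautiously, and defers stronger analyses to later phases. An interval is detail that an analysis plan may hold.

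Most of this stands. The sentence should not be struck, N = 40 is not wrong for its own test, and the 0.45 to 0.47 is only a scale for the imprecision.

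Two things remain. The article does more than leave the criterion open: Hypotheses fixes it as a comparison of observed means. And the listed strengths do not tell the reader that the sample was not sized for the one comparison that addresses natural course.

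A reader might also infer that reuse doubles the harm from any distortion at BL. A distortion common to both arms does move the contrast by twice its size (weights 0.5 + 1.5), but a plain arm comparison moves by the same amount (1 + 1), so this is not a cost of reuse.

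**Conclusion.** The point holds in a limited form. Reuse of the waitlist saves people, about 40 instead of 60, but adds little precision to treated-versus-natural change. At 20:20, r = 0.1 and no clustering, the variance is 92% to 100% of a plain 20 versus 20 comparison, and the 95% CI half-width is about 0.8 SD, as large as the effect used for planning.

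A reader might infer that reuse saves nothing. That would need an equal split, equal correlations and simple pooling together. The documents give one r for the time effect and no visible per-arm number, and optimal weighting, stronger serial correlation or more waitlist adolescents all give some gain. A reader might also infer that N = 40 is too small. For the pooled BL-FU test it reproduces.

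The sample size and the primary test are unaffected. What is at stake is how far a BL-FU reduction can be attributed to the programme.

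**What to change.** 1. In Strengths and limitations, keep the second strength but limit it to headcount for the BL-FU analysis. State that N = 40 was sized for the pooled time effect and not for the natural-course contrast.
2. In Hypotheses, replace the descriptive criterion with the estimated treated-minus-natural difference in change and its 95% CI, from a model with person-level covariance over PRE, BL and FU, so that the shared BL value is carried.
3. State the expected half-width (about 0.8 SD at r = 0.1 with 20 per arm), that it depends on r and the split, and that clustering by institution would widen it.

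This costs one extra exploratory model on data already collected and some wording. No patients, visits or procedures are added. The downside is that the natural-course check will look less favourable than a comparison of two means.

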## Conclusion

By developing the existing DELTA manual further in terms of setting-specific adaptions (DELTA-JU) for vulnerable adolescents suffering from SUDs, we may add another treatment option for this at-risk population. This requires evidence for acceptability, feasibility, and effectiveness as far as this exploratory trial is able to produce them. We hope that DELTA-JU can finally be disseminated within other institutions of youth welfare to help these adolescents to remain abstinent from alcohol and other drugs in the future.

## Ethics statement

This trial and all its procedures are in accordance with the Declaration of Helsinki. It has been submitted as an amendment to the DELTA evaluation study to the ethics committee of the University Hospital C. G. Carus Dresden and Technische Universität Dresden (approval in Jan 2022, number: EK 66022018 including amendments). It was furthermore pre-registered at the German Clinical Trials Register (DRKS, reference number: DRKS00027913, see www.drks.de/DRKS00027913), official as of 01.Feb 2022) where important protocol modifications will be communicated, see also SPIRIT 2013 checklist [75] (Supplementary information 1) and World Health Organization Trial Registration Data Set (Supplementary information 2) for details. An English version will be automatically uploaded to http://apps.who.int/trialsearch/. Both adolescent participants and personnel will have to consent to participate. In the case of adolescents aged 17 or younger, legal guardians as well have to agree to study participation by written consent after a comprehensive written and/or verbal information. Similar written information will be handed out to all participants, including information on study aims, procedures, duration, data security, voluntariness of participation and the right to leave the study at all times. Importantly, participants will be informed that any information on potentially illegal actions such as purchase, possession, sale, or use of illicit substances will not be forwarded to legal authorities, legal guardians or youth welfare institution personnel in accordance with data protection laws. Anonymity of study data will be assured by saving all information under an individual arbitrary ID code, with the linkage file between ID code and name only available to study personnel. All personnel including student assistants and master/doctoral candidates will undergo trainings on data security measures and good scientific practice as supervised by the principal investigators and/or the sponsoring institution. Study data will be hosted on servers of the funding institution (Technische Universität Dresden) in accordance with local data security laws. We do not seek to publish any identifying images or other personal or clinical details of adolescent participants that compromise anonymity. As for qualitative interviews of youth welfare institution personnel, we plan to publish anonymized sentences. Personnel will be informed in advance during the comprehensive written and/or verbal information, and will have to give written consent that they agree.

## Abbreviations

BL/FU/PRE: Assessments during the study at baseline, follow-up or previous to baseline
DRKS: German Clinical Trials Register
DELTA: Dresden multimodal therapy for adolescents with chronic substance use (German abbreviation)
DELTA-JU: The revised DELTA program for youth welfare institutions (JU = in Jugendwohneinrichtungen in German)
ICMJE: International Committee of Medical Journal Editors
ID: Personal identification number used to anonymize study data
MANOVA: Multivariate analysis of variance
SPIRIT: Standard protocol items: recommendations for interventional trials
SUD: Substance use disorders
WL: Waiting list control group (study arm/condition)
